#### Quantification of the association between short-term predicted AF risk and long-term AF and other diseases

We will include all patients randomly assigned to the testing dataset in CPRD-GOLD by the Mersenne twister pseudorandom number generator, categorised as lower or higher predicted AF risk by the developed prediction model at baseline (point of entry to the study). For long-term AF risk, we will plot Kaplan-Meier plots for individuals identified as higher and lower predicted risk of AF to assess the event rate for AF censored at 10 years, and calculate the hazard ratio (HR) for AF between higher and lower predicted risk of AF using the Cox proportional hazard model with adjustment for the competing risk of death. This will inform us of whether short-term AF risk is also associated with long-term AF risk, and whether an individual who undergoes risk-guided AF screening should be considered for repeated AF screening at a later time point (eg, 1 or 5 years).

For non-AF disease states, we will consider the initial presentation of a cardiovascular, renal or metabolic disease or death. This is because AF is not a disease in isolation and is known to be associated with a high risk of adverse clinical outcomes. To best characterise highly prevalent and morbid diseases, associated with the development or consequence of AF and that may be appropriate for prevention or targeted diagnostic pathways subsequent to AF screening (online supplemental figure 1),^9^ we will individually examine the following nine conditions: heart failure, valvular heart disease (and specifically aortic stenosis), myocardial infarction, stroke (ischaemic and haemorrhagic) or transient ischaemic attack, peripheral vascular disease, chronic kidney disease, diabetes mellitus and chronic obstructive pulmonary disease. These disease states have been further selected for investigation because interventions could be implemented and/or tested to reduce their clinical progression. We will also quantify the occurrence of death by any cause recorded in primary care or by death certification from the UK Death Register of the ONS, which will be mapped on to nine disease categories (online supplemental table 2). For each condition, a list of diagnostic codes from the CALIBER code repository, including from ICD-10th revision (used in secondary care) and Read coding schemes (used in primary care) will be defined comprehensively to identify diagnoses from EHRs. Incident diagnoses will be defined as the first record of that condition in primary or secondary care records from any diagnostic position. For the definition of new cases, we will exclude individuals for the analysis of each condition who had a diagnosis of that condition before the patient’s entry to the study. If no indication of a specific disease is recorded, then the patient will be assumed to be free from the disease. CPRD is a positive recording dataset, which reduces the likelihood of the non-recording of a clinically identified disease state.

We will create Kaplan-Meier plots for individuals identified as higher and lower predicted risk of AF to assess the event rate for non-AF outcomes censored at 10 years. We will derive the cumulative incidence rate for each outcome at 1, 5 and 10 years considering the competing risk of death, as well as death at 5 and 10 years. For each specified outcome, we will calculate the HR between higher and lower predicted risk of AF using Fine and Gray’s model with adjustment for the competing risk of death. We will also report adjusted HR where the model is adjusted for age, sex, ethnicity and the presence of any of the other outcomes at baseline. As some of the outcomes have incidence rates that are strongly associated with age (eg, aortic stenosis) or differ by sex (eg, heart failure),^39 40^ we will conduct subgroup analyses of incidence rates for higher and lower risk individuals for each outcome by age group (30–64 years and ≥65 years) and sex. As some of the non-AF outcomes are more likely to occur in the setting of prevalent AF (eg, stroke or heart failure),^9^ we will also conduct a sensitivity analysis whereby people with incident AF during follow-up are excluded.

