**Methods and analysis:**

We will investigate the application of random forest and multivariable logistic regression to predict incident AF within a 6-month prediction horizon, that is, a time-window consistent with conducting investigation for AF. The Clinical Practice Research Datalink (CPRD)-GOLD dataset will be used for derivation, and the Clalit Health Services (CHS) dataset will be used for international external geographical validation. Analyses will include metrics of prediction performance and clinical utility. We will create Kaplan-Meier plots for individuals identified as higher and lower predicted risk of AF and derive the cumulative incidence rate for non-AF cardio-renal-metabolic diseases and death over the longer term to establish how predicted AF risk is associated with a range of new non-AF disease states.

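### Long-term AF risk is to be read from Kaplan-Meier curves that ignore death as a competing event, and the AF hazard ratio's estimand is not identified

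*Protocol article*

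**What the plan says.** All of this is in the protocol article, mainly in the section on quantifying the association between short-term predicted AF risk and long-term AF and other diseases.

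- **Long-term AF, absolute risk.** The plan is that "we will plot Kaplan-Meier plots for individuals identified as higher and lower predicted risk of AF to assess the event rate for AF censored at"; the limit is 10 years. No other absolute-risk method is named for AF.
- **Long-term AF, relative measure.** The HR between higher and lower predicted risk is to be calculated "using the Cox proportional hazard model with adjustment for the competing risk of death".
- **Purpose.** The result is to show whether short-term risk also marks long-term risk, and it is to inform "whether an individual who undergoes risk-guided AF screening should be considered for repeated AF screening at a later time point (eg, 1 or 5 years").
- **Non-AF outcomes, plots.** "We will create Kaplan-Meier plots for individuals identified as higher and lower predicted risk of AF to assess the event rate for non-AF outcomes", again to 10 years.
- **Non-AF outcomes, estimates.** "We will derive the cumulative incidence rate for each outcome at 1, 5 and 10 years considering the competing risk of death", with HRs obtained "using Fine and Gray’s model with adjustment for the competing risk of death".
- **Abstract.** The aim there is to "derive the cumulative incidence rate for non-AF cardio-renal-metabolic diseases and death over the longer term". AF is not in that list.

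**The concern.** A person who dies without AF can no longer develop it. Kaplan-Meier with death treated as censoring acts as if such people stayed at the same future risk as survivors, so one minus the curve exceeds the proportion who will actually be diagnosed. The excess grows with mortality and with time. Age and disease history are candidate predictors, so the higher-risk group will probably be older and sicker. If its mortality is higher, its curve is inflated more and the two groups look further apart than they are.

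This matters most for AF. Whether to screen again after some years depends on how many people will develop AF by then, which is an absolute risk, and Kaplan-Meier is the only method the article names for it.

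The HR raises a separate problem. An ordinary Cox model with death censored gives a cause-specific HR. A Fine-Gray model gives a subdistribution HR. The article uses the same phrase about adjusting for the competing risk of death for a Cox model (AF) and for Fine-Gray (non-AF). A reader cannot tell whether the AF HR can be compared with the others.

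**Working it through.** **Is there a figure to reproduce?** No. The article gives no 10-year risk, no HR and no death rate for this analysis. The hazards below are assumptions, chosen only to show the size of the effect.

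**Formulas**, for a constant AF hazard a and death hazard d (per year) at time t:

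- One minus Kaplan-Meier, death censored: 1 − exp(−a·t)
- Cumulative incidence with death competing: a/(a+d) × [1 − exp(−(a+d)·t)]

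**Higher-risk group, a = 0.02, d = 0.06**, so a/(a+d) = 0.25:

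| Year | 1 − KM | Cumulative incidence | Excess (points) |
|---|---|---|---|
| 1 | 1 − e^−0.02 = 1.98% | 0.25 × (1 − e^−0.08) = 1.92% | 0.06 |
| 5 | 1 − e^−0.10 = 9.5% | 0.25 × (1 − e^−0.40) = 8.2% | 1.3 |
| 10 | 1 − e^−0.20 = 18.1% | 0.25 × (1 − e^−0.80) = 13.8% | 4.4 |

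At 10 years the relative inflation is 0.1813/0.1377 = 1.32.

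**Range for the higher-risk group at 10 years.**

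- With a = 0.02, the cumulative incidence is 16.5% for d = 0.02 and 12.6% for d = 0.08, so the ratio runs from 1.10 to 1.43.
- With a = 0.015, one minus Kaplan-Meier is 13.9% against 12.7% to 9.7% over the same d (ratio 1.10 to 1.44).
- With a = 0.03, it is 25.9% against 23.6% to 18.2% (ratio 1.10 to 1.43).

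Overall the inflation is about 10% to 44%, or 1.3 to 7.7 points. For the same hazards the excess is 0.35 to 2.4 points at 5 years and about 0.1 point or less at 1 year.

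**Lower-risk group, a = 0.002, d = 0.005 to 0.02, 10 years.** One minus Kaplan-Meier is 1.98% against 1.93% to 1.80%, an inflation of about 3% to 10% (0.05 to 0.18 points).

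**Effect on the contrast**, with a = 0.02, d = 0.06 against a = 0.002, d = 0.005. The higher:lower risk ratio by cumulative incidence and by one minus Kaplan-Meier is:

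- 1 year: 9.6 and 9.9
- 5 years: 8.4 and 9.6
- 10 years: 7.1 and 9.2

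This widening comes from the difference in mortality. With d = 0.02 in both groups, the 10-year inflation is 1.10 in each and the ratio hardly moves.

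**The hazard ratio.** Data were simulated with 30,000 people per group followed for 10 years. AF hazards were 1.5% and 0.2% a year and death hazards 5% and 1%. The true cause-specific HR is 0.015/0.002 = 7.5. Cox with death censored returned 7.5 and Fine-Gray 6.2. Both are correct for what they estimate, but they are different quantities.

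**The case against.** Four points can fairly be made for the plan.

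*Non-AF outcomes.* A reader might infer that every long-term estimate ignores death. The article does not support that. It plans competing-risk cumulative incidence at 1, 5 and 10 years and Fine-Gray HRs for these outcomes, and those are sound. What remains is that the Kaplan-Meier plots for the same outcomes would show higher values than the reported cumulative incidences.

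*The Cox model.* A reader might also infer that the Cox analysis inflates 10-year risk, or that it is definitely a plain Cox model whose HR differs in kind from the non-AF HRs. Neither follows. An HR is not an absolute risk, and Cox with death censored estimates a valid cause-specific HR. Fine-Gray is itself a proportional hazards model for the subdistribution, so the authors may have meant it for AF too. The fault that stands is an unidentified estimand.

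*All-cause death.* The article lists death separately when it sets out cumulative incidence, so it is not clear that a competing risk is meant to apply to it. The sentence assigning Fine-Gray to each outcome is loose on this point and would benefit from an explicit exception.

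*Size.* The example uses chosen hazards, and neither mortality by risk group nor the cut-off for higher risk is given in this section. At 1 year, one of the two repeat-screening times mentioned, the bias is negligible. The larger figures belong to 10 years. This stands, and it limits the weight of the point.

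**Conclusion.** The point holds for long-term AF. Followed as written, the plan would report AF risk from a method that overstates it whenever death competes, and would do so for a question that turns on absolute risk. The direction is certain if deaths are censored; the size is not. With 2% AF and 6% death a year assumed, the excess in the higher-risk group is 0.06 points at 1 year, 1.3 at 5 and 4.4 at 10. Greater inflation in the higher-risk group is probable but depends on its having higher mortality, which the article does not quantify.

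The AF HR needs a label rather than a different model. For non-AF outcomes the problem is confined to plots that would disagree with the planned estimates. Development and validation of the 6-month prediction model are not affected. The AF part should be corrected before analysis; the non-AF plots are a smaller matter of consistency.

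**What to change.** 1. Replace the Kaplan-Meier plots for AF and for each non-fatal outcome with Aalen-Johansen cumulative incidence curves, with death as the competing event.
2. Report AF cumulative incidence at 1, 5 and 10 years by predicted-risk group, as is already planned for the non-AF outcomes.
3. State whether the AF HR is cause-specific (Cox, death censored) or subdistribution (Fine-Gray), and reconcile the wording with the non-AF paragraph. Naming one is enough; reporting both for every outcome is optional.
4. Keep Kaplan-Meier and ordinary Cox for all-cause death, and say so.

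The cost is a few sentences and standard R functions, with no new data. The stated long-term AF risks will be somewhat lower.

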## Methods and analysis

### Data sources and permissions

The derivation dataset will be the Clinical Practice Research Datalink-GOLD (CPRD-GOLD) dataset. This is an ongoing primary care database, established in 1987, which comprises anonymised medical records and prescribing data contributed by general practices using Vision software. It contains data for approximately 17.5 million patients, with 30% of contributing practices in England, and represents the UK population in terms of age, sex and ethnicity.^16^ In order to contribute to the database, general practices and other health centres must meet prespecified standards for research-quality data (‘up to standard’).^16 20^

Recorded information includes patients’ demography, clinical symptoms, signs, investigations, diagnoses, prescriptions, referrals, behavioural factors and test results entered by clinicians, and other practice staff. All clinical information is coded using Read Codes.^21^ Extracted patients will have patient-level data linked to Hospital Episode Statistics (HES), Admitted Patient Care (APC) and Office for National Statistics (ONS) Death Registration. The CPRD dataset has been used to develop or validate a range of risk prediction models.^22^

The extracted dataset, including linked data, comprises all patients for the period between 2 January 1998 and 30 November 2018 from the snapshot of CPRD-GOLD in October 2019. Over this study period, the CPRD-GOLD dataset comprises approximately 2 million patients eligible for data linkage at an up-to-standard practice, with over 200 000 patients having a record of AF during follow-up.

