### Prediction model outcome ascertainment

The outcome of interest is first diagnosed AF or AFl after baseline. Baseline is taken in the CPRD-GOLD dataset as the first entry of the patient into the dataset. We have included AFl as an outcome since it has similar clinical relevance, including thromboembolic risk and anticoagulation guidelines, as AF.^5^ These will be identified using Read codes in CPRD dataset. For HES APC events and underlying cause of death variables in the ONS Death Registration data file, ICD-10 codes will be used. For CHS, events will be identified using ICD-9 codes. It should be noted that a report has estimated that 305 262 individuals in the UK have undiagnosed AF,^27^ and so incidence of AF within the study may be underestimated as there will be individuals with unrecorded asymptomatic AF.

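### A first myocardial infarction or stroke known only from the death certificate is counted as a competing death, not as the outcome, so the planned cumulative incidences are understated

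*Protocol article*

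**What the plan says.** The section of the protocol article on the association between short-term predicted AF risk and long-term AF and other diseases gives an explicit case definition for the non-AF conditions: "Incident diagnoses will be defined as the first record of that condition in primary or secondary care records from any diagnostic position". The description of the code lists has the same scope, "including from ICD-10th revision (used in secondary care) and Read coding schemes (used in primary care) will be defined comprehensively to identify diagnoses from EHRs". The acute conditions listed are "myocardial infarction, stroke (ischaemic and haemorrhagic) or transient ischaemic attack".

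Death certification appears in that section only for a separate outcome: "death by any cause recorded in primary care or by death certification from the UK Death Register of the ONS, which will be mapped on" (the target of the mapping is a set of nine categories in a supplemental table).

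The analysis then treats death as the competing event: "We will derive the cumulative incidence rate for each outcome at 1, 5 and 10 years considering the competing risk of death". For the group comparison, "we will calculate the HR between higher and lower predicted risk of AF using Fine and Gray’s model with adjustment for the competing risk of" (the competing event is again death). No exception is made for a death caused by the condition under analysis.

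The AF outcome is handled differently. Under Prediction model outcome ascertainment, "For HES APC events and underlying cause of death variables in the ONS Death Registration data file, ICD-10 codes will be used". Under Data sources and permissions, the linkage is confirmed: "Extracted patients will have patient-level data linked to Hospital Episode Statistics (HES), Admitted Patient Care (APC) and Office for National Statistics (ONS) Death Registration".

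**The concern.** Myocardial infarction and stroke can kill at first presentation. If the person dies before admission and the practice enters no diagnostic code, the only trace of the event is the certified cause of death. Under the stated definition that person never had the condition. The death then counts as something that prevented the condition from occurring, when it was the condition. In a Fine and Gray model the person also stays in the risk set as someone without the outcome.

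At stake are the absolute risks of myocardial infarction and stroke at 1, 5 and 10 years, which are a stated output. The article says these conditions were chosen because they may suit prevention or targeted diagnosis following AF screening. Fatal first events belong to that purpose, and the section itself sets out to study the initial presentation of disease. The plan also treats its outcomes unevenly, since death registration is a source for AF but not for these two conditions.

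**Working it through.** The article states no figure on this point, so there is nothing to reproduce. The check has two parts.

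**1. Following one patient through the text.** Take a person with no history who dies at home of a first stroke that is certified as the underlying cause, with no stroke code in the practice record.

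- Primary care source: no Read code for stroke.
- Secondary care source: no admission, so no Admitted Patient Care record.
- Death registration: stroke is the underlying cause, but this source is not in the definition.
- Status in the stroke analysis: no incident stroke; a competing death on the date of death.
- Status in the separate death outcome: a death, mapped to a disease category.

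No sentence carries the mapped cause of death back into the per-condition analysis.

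**2. Size, by illustration.** Let f be the share of first events known only from the certificate. All rates below are assumptions, because the article gives none.

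- Outcome hazard per year: 0.003 (lower predicted risk), 0.009 (higher).
- Hazard of death from other causes per year: 0.005 (lower), 0.04 (higher).
- Horizon: t = 10 years, constant hazards.

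True cumulative incidence is h/(h+d) × [1 − exp(−(h+d)t)].

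- Lower: 0.003/0.008 × [1 − exp(−0.08)] = 0.0288.
- Higher: 0.009/0.049 × [1 − exp(−0.49)] = 0.0712.

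Misclassification moves f × h from the outcome hazard to the death hazard. The total h + d is unchanged, so observed incidence is exactly (1 − f) times the true value in this model, at any horizon.

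| f (both groups) | Share of true value kept | Higher-risk group, 10 years |
|---|---|---|
| 5% | 0.95 | 6.8% |
| 10% | 0.90 | 6.4% |
| 20% | 0.80 | 5.7% |

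The true value in the higher-risk group is 7.1%.

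The subdistribution hazard ratio is approximated at 10 years by ln(1 − CIF higher) / ln(1 − CIF lower). The true value is 0.07381/0.02926 = 2.52.

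| f lower | f higher | Observed ratio |
|---|---|---|
| 5% to 20% | same | 2.52 to 2.51 |
| 5% | 15% | 2.25 |
| 10% | 20% | 2.23 |
| 10% | 30% | 1.94 |
| 20% | 10% | 2.84 |

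The last row reverses the third: incidences become 0.0288 × 0.80 = 0.0231 and 0.0712 × 0.90 = 0.0640, and 0.06618/0.02334 = 2.84. With equal shares the ratio hardly moves. With unequal shares it moves in whichever direction the inequality runs.

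**The case against.** Four arguments can be made for the plan.

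**Fatal events are captured elsewhere.** Deaths are taken from the register and mapped to disease categories, and the supplemental table with that mapping is not shown. This is true, and deaths could be reported by cause. But the article gives a positive case definition and states how death enters the analysis. Reporting deaths by cause alongside does not alter the per-condition incidence or the Fine and Gray model.

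**A practice may code the fatal event after death.** This stands. Such a code is a primary care record and the event would count. A reader might infer that every fatal event outside hospital is lost; the text does not support that. Only events with neither a practice code nor an admission are lost.

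**Disease diagnosed in care is a legitimate target.** For chronic kidney disease, diabetes or chronic obstructive pulmonary disease this is a fair description of what the study wants, and a death-certificate rule would place onset on the day of death. The argument stands for those conditions. It is weaker for myocardial infarction and stroke, where the fatal event can itself be the first presentation.

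**The size is unknown.** Also true. A reader might infer that the hazard ratio is pulled towards 1, on the ground that fatal first events are commoner in older and sicker people. The article gives no certificate-only share for either group. The opposite is arguable too, since higher-risk people may have more contact with care and so be more likely to have the event recorded there.

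**Conclusion.** The point holds for myocardial infarction and stroke. Followed as written, the plan counts a first event known only from the certificate as a competing death, and cumulative incidence of that condition is low by about f. The direction of this error follows from the definition. Its size depends on f, which the article does not give; the 5% to 20% range is an assumption.

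No bias of known direction in the hazard ratio is shown. A material change requires f to differ between the risk groups. The AF prediction model, its validation and the long-term AF analysis are not affected, and the point does not call for a change to the chronic conditions. This is a weakness in secondary analyses that is worth correcting because it is cheap to correct.

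**What to change.** In the section on long-term AF and other diseases, add wording along these lines after the case definition:

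*For myocardial infarction and stroke, an incident event is the first of a primary care record, a Hospital Episode Statistics Admitted Patient Care record, or an ONS death registration with the condition as underlying cause. An event found only in the death registration is dated at death. In the analysis of each of these outcomes, only deaths from other causes are competing events. The analysis restricted to primary and secondary care records is repeated as a sensitivity analysis.*

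Leave the definitions of the chronic conditions unchanged. It would also help to report how many first events come only from death registration, by predicted risk group. That count is f, and it would settle whether the hazard ratio is affected.

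No new data are needed, because death registration is linked and causes of death are already to be mapped. ICD-10 death codes for the two conditions must be specified, since the death categories may not isolate them. Certified causes of death are sometimes wrong, so some misclassification will enter; the sensitivity analysis shows how much the results depend on it.

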**Trial registration number:**

A systematic review to guide the overall project was registered on PROSPERO (registration number CRD42021245093). The study was registered on ClinicalTrials.gov (NCT05837364).

STRENGTHS AND LIMITATIONS OF THIS STUDYLarge and nationwide datasets representative of the community-dwelling populations in two countries.Predicting the risk of incident atrial fibrillation (AF) in the short term may be more useful to screening than longer prediction horizons.Quantification of the strength of association between predicted AF risk and other diseases may uncover other opportunities that could be actioned during AF screening beyond stroke prophylaxis.A calculator created from a parsimonious model may enhance the usability of the model in the real world and in contexts where electronic health records are unavailable or incomplete.It is estimated that more than a quarter of individuals living with AF are not diagnosed during routine care, which may mean that the performance of the prediction model may vary in a screening setting.

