### Research aim

The aims of this study are to:

Develop a model for predicting short-term AF risk from data routinely available in community-based EHRs.Quantify the association of predicted AF risk with a range of non-AF diseases.Externally validate the prediction model in an international context to assess transportability.Produce a calculator derived from a parsimonious prediction model.

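### The only hazard ratio planned for each non-AF disease is a Fine-Gray HR, which mixes disease rate with death rate; a cause-specific HR and a death HR are needed beside it to read strength of association

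*Protocol article*

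**What the plan says.** The second aim under Research aim is: "Quantify the association of predicted AF risk with a range of non-AF diseases". The strengths and limitations box gives the purpose: "Quantification of the strength of association between predicted AF risk and other diseases may uncover other opportunities" that could be acted on during AF screening.

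In the data analysis plan, the section on short-term predicted risk and long-term disease sets out these analyses for the non-AF outcomes:

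- Kaplan-Meier plots by risk group, "to assess the event rate for non-AF outcomes censored at 10 years".
- Absolute risk: "We will derive the cumulative incidence rate for each outcome at 1, 5 and 10 years considering the competing risk of death", plus death at 5 and 10 years.
- Relative measure: "For each specified outcome, we will calculate the HR between higher and lower predicted risk of AF using Fine and Gray’s model", with adjustment for competing death.
- An adjusted HR that adds age, sex, ethnicity and the other outcomes at baseline. No other hazard scale is named for it.

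A Cox model is named only for AF in the same section. That HR is to be obtained "using the Cox proportional hazard model with adjustment for the competing risk of death", which does not say whether it is cause-specific or subdistribution.

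**The concern.** A colleague reading an HR for, say, chronic kidney disease will usually take it as a ratio of disease rates among people who are alive and free of that disease. The Fine-Gray HR is not that. It keeps people who have died in the risk set, so it equals 1 when cumulative incidence is equal in the two groups. Cumulative incidence falls when more people die before they can develop the disease.

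The groups are split on predicted AF risk. Age is a candidate predictor, the cohort covers adults from about 30 upwards, and follow-up runs to 10 years. A sizeable crude difference in mortality is therefore foreseeable, although the article does not quantify it. In that case a modest HR could mean a modest association with the disease. It could equally mean a stronger association partly hidden by early death. The plan names no second HR that would tell the two apart, yet the result is meant to inform which diseases might be addressed alongside AF screening.

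**Working it through.** **Plan's own figure.** The article gives no HR, disease rate or mortality by risk group for this analysis, so there is nothing to reproduce. All rates below are assumptions.

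**Inputs.**
- Follow-up of 10 years, from the article.
- Assumed: 25% flagged as higher risk; disease rate 0.5% a year in the lower-risk group; mortality 0.5% a year in the lower-risk group and 1.5%, 3% or 5% a year in the higher-risk group; constant rates; administrative censoring at 10 years only.

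**Step 1: cumulative incidence.** With disease rate d and death rate m, 10-year cumulative incidence is d/(d+m) × (1 − exp(−10(d+m))).
- Lower risk: 0.005/0.010 × (1 − e^−0.10) = 4.76%.
- Higher risk, rate ratio 2.0, mortality 0.5%: 0.010/0.015 × (1 − e^−0.15) = 9.29%.
- Higher risk, rate ratio 2.0, mortality 3%: 0.010/0.040 × (1 − e^−0.40) = 8.24%.
- Higher risk, rate ratio 2.0, mortality 5%: 0.010/0.060 × (1 − e^−0.60) = 7.52%.

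The disease rate is the same in the last three lines; only mortality changes.

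**Step 2: approximate subdistribution HR at 10 years.** Use ln(1 − CIF higher) / ln(1 − CIF lower).
- Mortality 3%: ln(0.9176)/ln(0.9524) = 0.0860/0.0488 ≈ 1.76.
- Mortality 5%: ln(0.9248)/ln(0.9524) = 0.0782/0.0488 ≈ 1.60.

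**Step 3: the HR the model would fit.** Solving the population Fine-Gray score equation under the same assumptions gives:

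| True disease rate ratio | Mortality 0.5% | 1.5% | 3% | 5% |
|---|---|---|---|---|
| 1.0 | 1.00 | 0.95 | 0.88 | 0.81 |
| 1.5 | 1.50 | 1.43 | 1.33 | 1.21 |
| 2.0 | 2.00 | 1.90 | 1.77 | 1.61 |
| 3.0 | 3.00 | 2.85 | 2.65 | 2.41 |

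A reported HR near 1.6 is therefore compatible with a rate ratio of 1.6 and equal mortality, or with a rate ratio of 2.0 and mortality of 5% against 0.5% a year.

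**Step 4: other assumptions.** With disease at 0.3% a year, lower-risk mortality at 1% a year and 20% flagged, a true ratio of 2.0 becomes 1.95, 1.90, 1.73 and 1.44 at mortality ratios of 1.5, 2, 4 and 8. In simulation with equal disease rates and a mortality ratio of 4, the Fine-Gray HR was about 0.86 to 0.87, while the cause-specific Cox HR stayed at about 1.00.

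**Step 5: adjusted HR.** After age adjustment the mortality contrast should narrow. With a residual mortality ratio of 1.2 to 1.5 on a base of 1% a year, the Fine-Gray HR is 0.99 to 0.98 when the true ratio is 1.0, and 1.98 to 1.95 when it is 2.0.

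**The case against.** The strongest reply is that Fine-Gray is a deliberate and suitable choice. The risk flag is a prognostic label, not a causal exposure. The abstract itself says that cumulative incidence of disease and death will establish how predicted AF risk is associated with new disease states. For planning care after screening, how many flagged people will actually develop a disease, given that some die first, is a proper question. This stands: a reader might infer that the Fine-Gray HR is invalid here, and the documents do not support that.

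A reader might also infer that a disease unrelated to predicted risk will look protected, or that a real association will vanish. The first row of the table shows this is possible arithmetically. But the diseases were selected because they are linked to AF, and the article notes that some are strongly age-related. Crude disease rates are therefore likely to be well above equal in the flagged group, and the likely effect is attenuation with the direction kept.

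Nor does the article plan to rank diseases by HR, compare them with the AF HR, or apply a significance rule to them. Claims of distorted rankings or false-positive tests describe uses that the plan does not contain.

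The planned death figures, cumulative incidences and Kaplan-Meier plots would let a careful reader see the mortality contrast. That helps, but none of them is named as an HR on the disease-rate scale, and death from any cause is not the same as death without the disease in question. The adjusted HR reduces the problem without changing the scale.

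A condensed article can leave detail to a fuller plan. Here, though, the model is named, and naming it fixes the scale.

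**Conclusion.** The point holds as a limitation of using one scale, not as an error in the method. The unadjusted Fine-Gray HR for each non-AF disease will understate the ratio of disease rates if mortality is higher in the higher-risk group. Under the main assumed rates the shortfall is about 5% at 1.5% a year mortality, 12% at 3% and 20% at 5%, against 0.5% a year in the lower-risk group. It is larger at more extreme mortality ratios (2.0 appears as 1.44 at a ratio of 8). The adjusted HR is little affected if the residual mortality ratio is small. All of this depends on mortality by risk group, which the documents do not give.

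Whether the AF and non-AF HRs are on different scales cannot be settled from the text, because the wording for the AF model fits either reading. It needs stating. The all-cause death outcome is not affected, since nothing competes with it.

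**What to change.** In the section on predicted AF risk and other diseases:

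1. Keep the Fine-Gray HR and the cumulative incidences at 1, 5 and 10 years, and label that HR as an effect on cumulative incidence.
2. Add beside it, unadjusted and adjusted, the cause-specific Cox HR for each non-AF disease, with death treated as censoring, and the cause-specific HR for death without that disease.
3. For the AF outcome, state whether the Cox-based HR is cause-specific or subdistribution, and report AF and non-AF HRs on the same scales.

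This takes a few sentences of wording and standard models on data already in hand. The downside is one or two more HR columns per outcome, which have to be read together.
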